## Abstract

**Background:**

Tobacco use is a leading risk factor for premature mortality. Individuals with mental disorders exhibit a smoking prevalence twice that of the general population and engage in higher levels of tobacco consumption, thereby elevating their risk for tobacco-related health complications. Unlike with other substance use disorders, clinical practice in Germany neglects tobacco dependence as a risk factor prior to the initiation of psychotherapy, despite a clear need for intervention: Prolonged cigarette smoking exacerbates mental health symptoms and influences processes central to psychotherapy, such as implicit cognitive processes and emotion regulation. Moreover, short-term nicotine withdrawal associated with tobacco dependence can undermine motivation, reduce positive reinforcement, and cause emotional instability, potentially hindering efforts to improve mental health or the effectiveness of psychotherapeutic interventions. These factors underscore the importance of integrating smoking cessation strategies prior to formal psychotherapy to optimize the therapeutic process and patient outcomes.

This study investigates the effects of initiating an intensified smoking cessation program prior to starting psychotherapy. Main measure outcomes of interest are the degree of tobacco dependence, smoking behavior, and mental health outcomes in smokers with mental disorders. By addressing smoking behavior prior to therapy, this trial seeks to establish a more solid foundation for therapeutic work, potentially improving mental health outcomes and promoting a comprehensive approach to mental health care.

**Methods:**

A single-center randomized controlled trial in an outpatient psychotherapeutic clinic will examine the effects of an intensified smoking cessation intervention versus a waiting control condition. The primary outcome measures include smokers’ nicotine dependence, smoking behavior, and mental health symptoms related to their primary mental disorder, analyzed using variance analysis methods. The smoking intervention consists of a common guideline-based cognitive-behavioral program supplemented by a digital health application. Secondary outcomes include changes in self-reported self-efficacy and implicit cognitive biases. In addition, motivational measures, self-efficacy, implicit approach tendencies, and attitudes toward online interventions will be assessed as secondary measures and examined as potential predictors, moderators, or mediators in exploratory analyses. Attitudes toward online interventions will be measured once at baseline, while all other measures will be assessed before the intervention, post-treatment, and at 6-week and 6-month follow-up sessions.

**Discussion:**

Addressing smoking behavior before psychotherapy holds potential to significantly enhance mental health outcomes. This study investigates the integration of smoking cessation strategies prior to psychotherapeutic care for cigarette-smoking individuals with mental disorders. By aligning tobacco dependence treatment with approaches used for other substance use disorders, we aim to establish and discuss a comprehensive and guideline-conformant method. This strategy seeks to improve patient outcomes and a cohesive, integrated method for treating smokers with comorbid mental health disorders.

**Trial registration:**

Prospectively registered on ISCRTN on 01.05.2024, reference number ISRCTN12859609.

## Introduction

### Background and rationale {6a}

Tobacco use, recognized as the leading cause of preventable death worldwide [38, 73], presents a significant health risk to all, particularly to individuals with mental disorders due to their high smoking prevalence and consumption pattern. These individuals are nearly twice as likely to smoke as the general population [5, 59], often smoking more heavily [10] and relying on tobacco to cope with negative affect, rather than to gain pleasure [64]. This increased severity of tobacco use contributes to a drastically reduced life expectancy—up to 25 years shorter—for smokers with mental disorders compared to non-smoking individuals without mental disorders [13, 30, 44]. According to the World Health Organization [72], cigarette smoking remains the most common form of tobacco use. Notably, clinical practice for treating tobacco dependence among the population of smokers with mental disorders deviates from that for other substance use disorders. Despite the clear need for intervention, smoking cessation in individuals with comorbid mental disorders remains challenging, as evidenced by their persistently high smoking prevalence [5, 70].

The need for intervention in this specific population not only stems from proven fatal physical consequences resulting from prolonged tobacco consumption, but also from psychological and mental consequences. Nicotine, the primary alkaloid in tobacco responsible for the addictive potential of cigarette smoking, poses significant hazards to psychological well-being, making it particularly relevant in the treatment of smokers with mental disorders. When initiating psychotherapy, the professional code of conduct for psychotherapists in Germany mandates prioritizing abstinence within the initial ten sessions if a patient meets diagnostic criteria for substance dependence or abuse [62]. However, tobacco dependence or abuse is excluded from these regulations. This is surprising given the existing research on nicotine’s impact on mental health symptoms as well as evidence highlighting nicotine’s influence on neuropsychological processes. Looking at nicotine’s impact on mental health, research shows associations of smoking and a decline in mental health symptoms, such as reduced quality of life [56], poor sleep quality [31], and higher rates of depressive and anxiety symptoms [12, 25, 48]. Among smokers with mental disorders, tobacco consumption may exacerbate mental health symptoms, while psychological distress can intensify smoking, creating a vicious cycle. Recent meta-analyses have indicated that successful tobacco cessation has long-term positive effects on mental health, as indicated by reduced symptoms of depression and anxiety, as well as overall increased quality of life [14, 63], and that these positive effects are comparable or even superior to those following pharmacological antidepressant treatment [63].

Nicotine withdrawal, which occurs not only during deliberate cessation, but also is experienced by regular smokers during intervals when nicotine levels decline due to its short half-life, and smoking is not immediately feasible, further complicates the picture by negatively affecting cognitive and emotional processes. Nicotine withdrawal is linked to memory deficits [55], concentration difficulties and increased impatience [28], and impulsivity and impaired decision-making [35]. Such cognitive impairments can hinder the patient's engagement with cognitive-behavioral techniques, emphasizing the need to address smoking before psychotherapy begins. Additionally, nicotine withdrawal reduced neurobiological reward sensitivity with diminished responses to positive stimuli persisting for several days [19, 35]. In the context of patients aiming to initiate psychotherapy, a diminished reward system due to prolonged tobacco smoking may reduce the motivation and positive reinforcement essential for behavioral change. Furthermore, the cyclical nature of withdrawal can cause emotional dysregulation and mood instability [43], potentially reducing therapy adherence and overall treatment engagement.

Building on the understanding of how nicotine withdrawal impairs cognitive and emotional functioning, it is also crucial to consider the broader neuropsychological effects of nicotine use, particularly in the context of patients aiming to undergo psychotherapy. Research suggests that nicotine, like other psychoactive substances such as alcohol, can significantly affect learning processes relevant to psychotherapy. So-called dual-process models of addiction (e.g. [68]) provide a useful framework for understanding these processes. According to these models, tobacco dependence can be described as a result of interactions between a reflective system and an impulsive system. The reflective system encompasses deliberate, goal-directed decision-making and self-regulation, while the impulsive system—driven by associative learning and emotional responses—manages automatic cravings triggered by stimuli and conditioned responses from repeated nicotine use, often referred to as implicit processes [17]. Implicit processes play a crucial role in maintaining tobacco dependence. Research supports this model by demonstrating that prolonged tobacco consumption is linked to cognitive biases associated with these implicit processes. For example, prolonged tobacco use is associated with attentional biases towards smoking-related cues [22], approach biases (e.g., [41, 67]), and interpretation biases [40]. Taken together, current research shows that prolonged tobacco use is linked to declines in mental health, cognitive and emotional impairments, and the development of cognitive biases and automatic action tendencies. Integrating smoking cessation strategies prior to psychotherapeutic treatment could thus enhance mental health outcomes and increase patient receptivity by mitigating nicotine-related neuropsychological disruptions that undermine the effectiveness of interventions dependent on cognitive and emotional engagement.

Despite this clear benefit, however, clinical practice in Germany still faces significant challenges in effectively addressing tobacco dependence among patients with comorbid mental disorders [5]. The national Association of the Scientific Medical Societies in Germany (AWMF) guideline for tobacco-related disorders [5] recommends that smokers with comorbid mental disorders receive the same smoking cessation interventions as those offered to the general population. These include pharmacological treatments (for an overview see [28]), cognitive–behavioral therapy (CBT)-based interventions (e.g., [37]), smartphone-based self-help programs (e.g., [54]), or multimethod approaches (e.g., [24]), with clinical consensus indicating that more complex and intensive smoking cessation programs may yield better outcomes and long-term abstinence for smokers with comorbid mental disorders [45].

In summary, research consistently highlights the detrimental effects of smoking on mental health, particularly on emotional, cognitive, and implicit processes, which is especially relevant in the context of psychotherapy and a holistic approach to mental health. At the same time, there is a notable gap in addressing tobacco dependence among psychotherapeutic patients [5]. In light of these gaps, the current study seeks to investigate the effects of an intensified smoking cessation program for smokers with mental disorders, implemented prior to starting formal psychotherapy. By this, our study seeks to align the standard treatment of tobacco dependence with the approach taken for other substance use disorders within the context of psychotherapeutic care in Germany. By targeting smoking behavior before the commencement of psychotherapy, we aim to establish a more solid foundation for therapeutic work, improving patient outcomes prior to the initiation of psychotherapy for the treatment of the primary mental disorder.

To this end, we employ a multifaceted smoking cessation intervention that combines face-to-face sessions with licensed psychologists and an additional digital health application. We will evaluate the effects of this approach on tobacco dependence, smoking behavior, and mental health outcomes related to the primary mental disorder. Additionally, the study will examine predicting, moderating, or mediating factors such as motivation to quit, willingness to change, self-efficacy, and attitudes towards online interventions to understand their influence on treatment and inform secondary analyses. To integrate both reflective and implicit cognitive processes, we are also incorporating the Approach-Avoidance Task (AAT; [53]) as an additional measure for implicit processes associated with tobacco dependence. The task has been proven effective in assessing and altering drug-related approach biases for substances like alcohol [69], cannabis [15] and recently, for tobacco [39, 42, 61]. By incorporating the AAT in our study, we aim to measure implicit cognitive biases related to smoking and how they change in response to smoking cessation treatment, thereby advancing the understanding of how addressing smoking prior to psychotherapy affects patients. By integrating smoking cessation into standard psychotherapeutic care, we aim to offer new insights into its potential benefits and emphasize the importance of incorporating smoking cessation as a critical component of comprehensive mental health treatment.

### Objectives {7}

We expect a treatment effect of the intensified smoking cessation on variables regarding tobacco dependence severity, smoking behavior as well as mental health outcomes, as evidenced by a reduced nicotine dependence severity, reduced smoking intensity, a higher quality of life and subjective psychological well-being, and reduced perceived impairment of mental health symptoms and depressive symptoms in patients in the experimental condition receiving a smoking cessation intervention than in patients in the wait-list-control condition. These changes are expected to become apparent both in the short-term (i.e., post-treatment) as well as the long-term (i.e., 6 weeks and 6 months follow-up) when compared to the baseline measures.

### Trial design {8}

The present research project demonstrates a single-center randomized controlled trial examining the impact of an intensive smoking cessation treatment compared to a waiting control condition on tobacco dependence and mental health symptoms related to the primary mental disorder among smokers aiming to initiate outpatient psychotherapy. All participants included in the study are receiving three psychotherapeutic consultations and fulfill an indication for psychotherapy. We chose to include a waiting control condition instead of an active (unspecific) control condition for comparison as a waiting control condition mirrors the typical course for patients awaiting psychotherapy, making the findings more applicable to real-world clinical settings. Eligible participants will be randomly assigned to either the experimental condition (immediate diagnostic session, a six-session smoking cessation program and a self-guided digital health application) or the waiting control condition (diagnostic sessions only). Patients randomly assigned to the control condition will be placed on a wait-list and will receive the smoking cessation intervention after 6 months. Post-treatment assessments for the intervention group will occur three weeks after their initial diagnostic session, which marks the end of the treatment phase. Similarly, participants in the control condition will undergo post assessments 3 weeks after their initial diagnostic session. Follow-up assessments for both groups will take place at 6 weeks (follow-up 1) and 6 months (follow-up 2) after the completion of the post-treatment assessments.

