Additionally, personalized recommendations tailored to each individual’s smoking behavior will be provided. Detailed descriptions of the individual sessions are outlined in the manual by Batra and Buchkremer [4]. In this research project, we will augment the original program by increasing session frequency and incorporating a self-help smoking cessation smartphone application to address specific challenges faced by smokers with mental disorders. While the original program was designed with weekly sessions over a course of 6 weeks, our intensified version will include two sessions per week, shortening the intervention duration to three weeks. Furthermore, participants will have access to the digital health application (*NichtraucherHelden®*,Sanero Medical GmbH, Stuttgart, Germany), a CBT-based self-help app featuring eight modules of psychoeducation, tasks, and relapse prevention. Recent evidence from a nationwide, multicentric, parallel, randomized controlled trial demonstrated the app’s feasibility and efficacy, with the intervention condition showing twice the abstinence rates at a 7-day point prevalence compared to the control condition [54].

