### Participant timeline {13}

Smoking patients who have had three psychotherapeutic consultations at the Psychotherapeutic Outpatient Center of the University of Siegen will be informed about the option of participation in the current study. Interested participants will be contacted by the study team and undergo a telephone interview to determine eligibility and fulfillment of the inclusion criteria (*− t*_1_). Following telephone screening for a duration of 10–30 min, patients will be invited to the first smoking cessation session, during which informed consent will be obtained and psychological symptoms will be assessed within the course of a diagnostic session (baseline, *t*_*0*_). After the diagnostic session, during which all baseline measures will be assessed, patients will be randomly assigned either to the experimental group or the passive control group. The experimental condition will receive a 6-step smoking cessation program and additional access to a smartphone-based self-help application. The duration of the intervention will be three weeks. Afterwards, patients will be invited again to assess all measures of interest (*t*_1_). Six weeks (*t*_2_) and 6 months (*t*_3_) after completion, patients will be invited once again for follow-up assessments. The participants’ timelines and data assessment points are shown in Table 2..

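### The start of the controls' six-month wait is not fixed, so up to the whole three-week programme could precede their 6-month assessment (t3)

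*Protocol article*

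**What the plan says.** The protocol article gives the following timings.

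- **Control programme** (Trial design {8}): "Patients randomly assigned to the control condition will be placed on a wait-list and will receive the smoking cessation intervention after 6 months". No starting point for the six months is given.
- **Allocation** (Participant timeline {13}): "After the diagnostic session, during which all baseline measures will be assessed, patients will be randomly assigned". Wait-listing therefore happens just after t0.
- **Post-assessment, t1** (Trial design {8}): "participants in the control condition will undergo post assessments 3 weeks after their initial diagnostic session".
- **Follow-up 2, t3, both arms** (Trial design {8}): "6 months (follow-up 2) after the completion of the post-treatment assessments". Outcomes {12} and Participant timeline {13} agree.
- **Programme length** (Intervention description {11a}): "two sessions per week, shortening the intervention duration to three weeks".
- **Content of the control arm** (Trial design {8}): "the waiting control condition (diagnostic sessions only").

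Objectives {7} expects a difference between the experimental and wait-list arms in "the long-term (i.e., 6 weeks and 6 months follow-up) when compared to the baseline measures". Statistical methods {20a} uses t3 as one of the four time levels in the repeated-measures ANOVA of each continuous primary outcome. The same section compares abstinence rates by chi-squared tests at post-treatment and follow-up.

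**The concern.** The wait is described as six months, but t3 is six months plus three weeks after baseline, and three weeks is the length of the programme. If the wait is counted from the moment a patient joins the wait-list, a control can be offered and can complete all six sessions before t3. For that patient, t3 would sit where t1 sits for an experimental patient, at the end of treatment.

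The long-term hypothesis needs a comparison of treated with untreated patients at t3. Otherwise the 6-month contrast on all eight primary outcomes compares patients treated about six months earlier with patients who are in treatment or have just finished it.

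Nothing else in the article would catch this. The covariates in the choice-of-comparators section {6b} cover other psychotherapeutic and psychopharmacological treatment and do not name the trial's own programme given to controls. The multiple imputation in {20c} deals with missing values, whereas a t3 value measured after the programme has begun is observed and would enter the intention-to-treat analysis as ordinary control data.

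**Working it through.** **Dates.** One month is taken as 365.25/12 days, so 6 months = 182.625 days = 26.09 weeks. All times count from t0.

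- t1 = 21 days = week 3.
- t2 = 21 + 42 = 63 days = week 9.
- t3 = 21 + 182.625 = 203.625 days = week 29.09. This follows the plan's own definition (t1 + 6 months), and the three sections that define t3 agree on it.

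**Start of the controls' programme (21 days long) under each reading.**

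| Six months counted from | Start (week) | Earliest end (week) | t3 minus start | t3 minus end |
|---|---|---|---|---|
| Allocation, just after t0 | 26.09 | 29.09 | 3.0 weeks | 0.0 weeks |
| t1 | 29.09 | 32.09 | 0.0 weeks | −3.0 weeks |

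On the first reading the whole programme fits before t3. On the second, start and t3 fall together, and the overlap is zero only if t3 is measured first. If the phrase means that controls start once the 6-month assessment is done, the overlap is also zero. The range is 0 to 3 weeks.

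**Effect on the t3 contrast (illustration).** Let c be the share of controls treated before t3. Assume that they then show the same mean outcome as the experimental arm. The expected difference is (1 − c) × the true difference. The documents give no value for c, so the range is 0 to 1: half is lost at c = 0.5 and all at c = 1.

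For power at t3, assume a true standardised difference d = 0.5, 31 per arm and two-sided 0.05. By normal approximation, power = Φ(d·√(31/2) − 1.96).

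- c = 0: d = 0.5, Φ(1.968 − 1.96) = 0.50.
- c = 0.25: d = 0.375, Φ(1.476 − 1.96) = 0.31.
- c = 0.5: d = 0.25, Φ(0.984 − 1.96) = 0.16 to 0.17 (0.165).

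**Effect on the condition × time test (illustration).** Assume N = 62 and a common correlation of 0.5. With group differences δ at t0 to t3, λ = (N/4)·Σ(δ − mean δ)²/(1 − 0.5), on 3 and 180 degrees of freedom.

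- δ = (0, 0.5, 0.5, 0.5): λ = 5.81, power 0.49.
- δ = (0, 0.5, 0.5, 0.25): λ = 5.33, power 0.46.
- δ = (0, 0.5, 0.5, 0): λ = 7.75, power 0.63.

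In this example, losing the whole t3 difference makes the interaction easier to detect, because the profile then varies more over time. A significant interaction would therefore not show that the 6-month comparison was intact.

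The planned sample size of 62 is not affected by this point.

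**The case against.** A reader might infer that the protocol contradicts itself and that, as written, the 6-month comparison is one of early against just-completed treatment. The documents do not support that.

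- The anchor of the six months is not stated. Counting from allocation is the plain reading, but it is a reading.
- The article often uses six months as the label for the last assessment, whose nominal name leaves out the three-week treatment phase. The wait may simply mean until that assessment is done.
- The control condition is defined as diagnostic sessions only, and both follow-ups are scheduled for both groups. This fits an intention to measure t3 before controls start.
- The participant timeline (Table 2) is not available in the text reviewed and may settle the order. Its absence is not a fault of the plan.
- Even counted from allocation, six months sets only an earliest start. Complete overlap needs a prompt start and six sessions kept to schedule.

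A second tempting inference is that the overlap would reverse a real effect. The dilution formula cannot do that, since it shrinks the difference to zero at most. Reversal needs a further assumption, such as relapse in the experimental arm by six months, which the plan does not quantify. Nor is the direction certain for every outcome: the adverse-event section {22} says withdrawal symptoms usually subside within 2 to 3 weeks, so some controls could be measured while still affected.

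These objections remove the claim of a proven contradiction. They do not remove the gap: no section shown gives the starting point or says that a control's t3 precedes the first cessation session. Nor is this a detail that an article can leave to a fuller document, because the article states both timings and, on their plain reading, they do not fit together.

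**Conclusion.** The point holds as an unresolved ambiguity in the design, with moderate confidence. Between none and all of the controls' three-week programme can fall before t3, depending on where the six months start and in which order the two events occur.

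If there is overlap, the 6-month contrast, the abstinence test at follow-up 2 and the t3 level of the ANOVAs no longer compare treated with untreated patients. The simplest consequence is bias towards zero in proportion to the share of controls already treated. That rests on the assumption that those controls respond as the experimental arm does. The power figures rest further on the assumed d = 0.5 and serve only as illustration.

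The assessments at t1 (week 3) and t2 (week 9) precede any control treatment on every reading, so the short-term hypothesis and the first follow-up stand.

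**What to change.** 1. Reconcile Trial design {8}, Outcomes {12}, Participant timeline {13} and the timeline table, so that the starting point of the six months and its order relative to the control t3 assessment are stated once and without ambiguity. Which timing applies is for the investigators to decide.
2. Record the date of each control's first cessation session next to the date of that patient's t3 assessment.
3. Pre-specify that a control t3 value recorded after that session is flagged and not analysed as untreated control data in the t3 contrast.
4. State what happens if many values are flagged. If most control t3 values are affected, the chained-equation imputation has no untreated t3 data to learn from. The randomised long-term claim should then be limited to t2.

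The cost is a clarified sentence, one recorded date per control and one analysis rule, with no extra patients or visits. It should be done promptly: the trial status section says that data collection began in August 2024 and ends by April 2027, and an untreated t3 value cannot be recovered once the control's programme has started.
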